## Abstract

**Background:**

This study will test the uptake and effectiveness of a flexible package of smoking cessation support provided primarily by the practice nurse (PN) and tailored to meet the needs of a diversity of patients.

**Methods/Design:**

This study is a cluster randomised trial, with practices allocated to one of three groups 1) Quit with Practice Nurse 2) Quitline referral 3) GP usual care. PNs from practices randomised to the intervention group will receive a training course in smoking cessation followed by access to mentoring. GPs from practices randomised to the Quitline referral group will receive information about the study and the process of written referral and GPs in the usual care group will receive information about the study. Eligible patients are those aged 18 and over presenting to their GP who are daily or weekly smokers and who are able to give informed consent. Patients on low incomes in all three groups will be able to access free nicotine patches.

Primary outcomes are sustained abstinence and point prevalence abstinence at the three month and 12 month follow-up points; and incremental cost effectiveness ratios at 12 months. Process evaluation on the reach and acceptability of the intervention approached will be collected through Computer Assisted Telephone Interviews (CATI) with patients and semi-structured interviews with PNs and GPs.

The primary analysis will be by intention to treat. Cessation outcomes will be compared between the three arms at three months and 12 month follow-up using multiple logistic regression. The incremental cost effectiveness ratios will be estimated for the 12 month quit rate for the intervention groups compared to usual care and to each other. Analysis of qualitative data on process outcomes will be based on thematic analysis.

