#### Primary outcomes

Uptake of the intervention in each group and characteristics of patients - age, sex, language spoken at home, ethnicity, education levels, occupation, smoking history, level of smoking and nicotine dependence.

Smoking cessation rates: sustained abstinence defined as patients reporting abstinence of ≥ one month at the three month follow-up and ≥ 10 months at the 12 month follow-up; and point prevalence abstinence defined as ≥ seven days of sustained abstinence at the three month and 12 month follow-up points. Validation of smoking cessation will not be undertaken as reviews confirm the accuracy of self-report measures, and conclude that validation is unnecessary in trials where there is no strong association between the interviewer and respondent [43]. Number and duration of quit attempts will be a further outcome measure as it is known that the key effect of advice from a health professional is to encourage the smoker to try to quit [10,11].

Health economic outcomes: the economic evaluation will compare the flexible support intervention 'Quit with Practice Nurse' and the 'Quitline referral intervention' with standard 'in practice management by the GP' (control group.) Cost analysis will be from the perspective of the health care sector and include direct costs of the intervention, including for recruitment, and for the intervention (GP costs, practice nurse costs, nurse training costs, telephone counseling costs, pharmaceutical costs, and overheads such as room rents).

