#### Data Analysis

Analysis for the primary outcomes of sustained abstinence and point prevalence abstinence will be on an intention to treat basis with cases retained regardless of whether they accept or receive the intended intervention. A series of planned imputation strategies for missing data will be used in examining outcomes for missing data. These are 1) analysis will be done on all participating patients, where all patients with missing outcome data will be assumed to be smokers; 2) the last known value carried forward to replace the missing value; 3) an analysis of outcomes for patients with complete outcome data. We will compare cessation outcomes between the three arms at three months and 12 month follow-up using multiple logistic regression. This approach will allow us to adjust for clustering and to assess the effect of potential confounders such as age, sex, socioeconomic status, ethnicity, language spoken at home and nicotine dependence on cessation outcomes.

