#### Health economic analysis

The study will estimate incremental cost effectiveness ratios (ICER) of cost per quitter for brief advice and referral to Quitline, and with the flexible support intervention, compared to standard GP care. The ICER will be estimated for the 12 month quit rate for the intervention, less an unaided/natural quit rate. Adjustments to effect sizes will also be made for long term relapse rate among the 12 month quitters.

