#### Sample size

The observed 12 month sustained abstinence outcomes of GP usual care and Quitline referral in Borland et al.'s study in Victoria were 2.6% and 6.5% respectively [16]. The sustained abstinence at six months in a pilot study of practice nurse support was 16%. Assuming this drops to 12% at 12 months we have calculated power to detect a 5.5% difference in sustained abstinence quit rates between 'Quit with Practice Nurse' intervention versus the referral intervention and a 9.4% difference between 'Quit with Practice Nurse' intervention and the usual care control group at one year follow up with 80% power at the 5% significance level. Before adjustment for clustering this requires 471 patients per group to detect the 5.5% difference and 140 per group to detect the 9.4% difference (calculations using STATA software). To adjust for clustering the intracluster correlation coefficient observed by Lennox et al. in a smoking cessation trial in general practice has been used. The intracluster correlation coefficient observed in this study was 0.013 [45]. The resulting design effect = [1+ (size of cluster-1) × intracluster correlation]. In this study we plan to recruit 25 patients per practice so the design effect is 1.31 so the number per arm is 471 × 1.31 = 617 giving a total sample size of 1851. To enroll these participants we will recruit 90 general practices and 2250 patients across New South Wales and Victorian study locations (to allow for approximately 10% drop out rate of practices) and randomise 30 practices to each arm of the study.

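### Four cessation endpoints are all primary and none ranks first, although the trial is sized on only one of them, 12-month sustained abstinence

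*Protocol article*

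**What the plan says.** **Primary outcomes.** The abstract lists them in the plural: "Primary outcomes are sustained abstinence and point prevalence abstinence at the three month and 12 month follow-up points", together with 12-month incremental cost-effectiveness ratios (ICERs). The Primary outcomes section repeats both abstinence definitions at both times, including "point prevalence abstinence defined as ≥ seven days of sustained abstinence at the three month and 12 month follow-up points". It opens with another item, "Uptake of the intervention in each group and characteristics of patients", which the abstract does not list as primary, and ends with the health economic outcomes. Neither place says which outcome comes first.

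**Analysis.** The Data Analysis section again calls both abstinence definitions primary and adds: "We will compare cessation outcomes between the three arms at three months and 12 month follow-up using multiple logistic regression". For the economic outcomes the wording is one of estimation: "The study will estimate incremental cost effectiveness ratios (ICER) of cost per quitter". No test is given for uptake.

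**Sample size.** Only 12-month sustained abstinence is used, at assumed rates of 12% (practice nurse), 6.5% (Quitline referral) and 2.6% (usual care). Two contrasts are powered, nurse against referral and nurse against usual care, "with 80% power at the 5% significance level". That is the only place where a significance level appears.

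**The concern.** Two abstinence definitions at two times give four primary cessation endpoints. With three arms there are up to three pairwise contrasts per endpoint, two of which are powered. Unless one endpoint is named, the article leaves open which result decides whether the nurse model worked. A reader could accept a three-month difference, or a seven-day difference at 12 months, as a positive primary result even if sustained abstinence at 12 months did not differ.

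The article's own background shows that the time points can disagree. In the earlier Quitline referral trial it cites, sustained abstinence differed by 12.3 − 6.9 = 5.4 points at three months and by 6.5 − 2.6 = 3.9 points at 12 months, and the article says the latter did not reach significance. The Discussion in the abstract looks ahead to the nurse model becoming the preferred one in Australian general practice, so the deciding endpoint should be fixed in advance.

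**Working it through.** **1. Reproduce the sample size.** Inputs from the Sample size section: 12% against 6.5%, 12% against 2.6%, alpha 0.05, power 0.80. Formula for two proportions:

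n₀ = [z₀.₉₇₅ √(2p̄q̄) + z₀.₈₀ √(p₁q₁ + p₂q₂)]² / Δ², then with continuity correction n = (n₀/4) [1 + √(1 + 4/(n₀Δ))]².

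| Contrast | Two-sided, corrected | Two-sided, uncorrected | One-sided, corrected | Article |
|---|---|---|---|---|
| 12% vs 6.5% | 471 | 435 | 378 | 471 |
| 12% vs 2.6% | 140 | 120 | 114 | 140 |

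Of these variants, only the full two-sided 5% for each contrast, with continuity correction, gives the article's figures. No alpha was shared between the two contrasts. Design effect: 1 + 24 × 0.013 = 1.312; 471 × 1.31 = 617 per arm; 3 × 617 = 1851. All agree with the article.

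**2. Familywise error if any primary cessation result may carry the claim.** Assumptions: no true difference on any endpoint; normal test statistics in three equal arms; four equally correlated endpoints; each test at two-sided 5%. Contrasts that share an arm are correlated through it. The article gives no endpoint correlation, so it is varied. Simulated chance of at least one significant result:

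| Endpoint correlation | One contrast (4 tests) | Two powered contrasts (8 tests) | All three contrasts (12 tests) |
|---|---|---|---|
| 0 | 19% | 32% | 41% |
| 0.5 | 16% | 27% | 34% |
| 0.7 | 13% | 23% | 29% |
| 0.9 | 9% | 16.5% | 22% |

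The formula for independent tests, 1 − 0.95¹² = 46%, does not apply: the three contrasts share arms, which caps the figure at about 41% even with uncorrelated endpoints.

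**3. The same for 12-month sustained abstinence alone.** About 9% for the two powered contrasts and 12% for all three. Naming one endpoint removes most of the excess, but the contrasts still need a rule.

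**4. What each remedy costs.** Bonferroni over the two powered contrasts (alpha 0.025 each) raises 471 to 563, and 563 × 1.31 ≈ 738 per arm, about 2,213 in total against 1,851. Two procedures avoid this:

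- *Gatekeeper.* Test the overall arm effect (2 degrees of freedom) at 5%, and only if it is significant test the pairwise contrasts at 5% each. With three arms, any two pairwise nulls together imply the global null, so this is a closed test. Simulated familywise error under the global null was 5.0%. With 471 effectively independent patients per arm at the article's rates, the overall test was significant in over 99.9% of runs, and power for nurse against Quitline (uncorrected test) was 83.6% with or without the gate.
- *Fixed sequence* of the two powered contrasts, each at 5%. If nurse against usual care comes first, that step needs only 140 per group before clustering, so at 471 it is passed almost surely at the assumed rates.

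**The case against.** **The powered endpoint can be identified.** The Sample size section uses 12-month sustained abstinence and two contrasts only, and the cessation hypothesis concerns the nurse arm. This stands in part: it shows what the investigators sized for, and it makes the two-contrast column more relevant than the three-contrast one. It does not make that endpoint the primary one, because three other places give all four equal standing.

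**Adjustment may be in an analysis plan not shown.** This also stands in part. A full 5% per contrast is demonstrated for the sizing and only inferred for the analysis, and silence on adjustment is not itself the defect. But which outcomes are primary is settled in this article, in the plural.

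**The inflation needs a rule that any endpoint wins.** True. If the claim required both nurse contrasts to succeed on one named endpoint, there would be no inflation. With one contrast and a correlation of 0.9 the error is only about twice nominal.

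A reader might also infer three stronger things that the article does not support:

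- *That uptake and ICERs add to the error rate.* They are called primary, but ICERs are to be estimated and uptake has no test, so neither is counted here.
- *That there is one inflation figure.* Any single value rests on a correlation the article does not give.
- *That the earlier Quitline trial shows early and point-prevalence differences to be easier to obtain.* The fall from 12.3% to 6.5% is a change in quit rate within the referral arm, not a between-arm difference, and the figures say nothing about point prevalence.

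**Conclusion.** The point holds in this form: four cessation endpoints are primary and unranked, the trial is sized on one, and each of the two powered contrasts has the full two-sided 5%. If any of the four may carry the claim at 5%, the familywise error is about 16% to 32% over the two powered contrasts, roughly three to six times nominal, and 22% to 41% over all three, roughly four to eight times. The ranges rest on an assumed equal endpoint correlation from 0.9 down to 0, the global null, and a decision rule that the article neither states nor excludes. That the final analysis will be unadjusted is not established. That the article fails to say which endpoint decides is established by its own text.

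**What to change.** 1. Name sustained abstinence at 12 months as the single primary endpoint, matching the Sample size section.
2. Fix one procedure for the contrasts without splitting alpha: either the overall 2-degree-of-freedom test at 5% followed by the pairwise contrasts at 5% only if it is significant, or a stated fixed sequence of the two powered contrasts. The first also covers Quitline against usual care; under the second that contrast would be secondary. Either should use the clustering-adjusted model.
3. Make three-month sustained abstinence and both point-prevalence outcomes secondary, and report uptake and ICERs as estimates with intervals.
4. Align the abstract, Primary outcomes and Data Analysis sections, including whether uptake is on the primary list.

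The cost is wording; the 617 per arm need not change. The claim of almost no power loss depends on the assumed rates: if usual care came closer to the nurse arm than 2.6% against 12%, the first step of either procedure would be harder to pass. The real price is that three-month and seven-day results could no longer be headline primary claims.

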**Discussion:**

High quality evidence on effectiveness of practice nurse interventions is needed to inform health policy on development of practice nurse roles. If effective, flexible support from the PN in partnership with the GP and the Quitline could become the preferred model for providing smoking cessation advice in Australian general practice.

**Trial Registration:**

ACTRN12609001040257

## Background

Tobacco remains the most common preventable cause of death in the world today. The World Health Organization estimates that tobacco killed 5.4 million people globally in 2008 and on current trend this will rise to 8 million deaths per year by 2030 with more than 80% of deaths occurring in the developing world [1]. Despite reduction in prevalence of smoking in the Australian population, tobacco use and dependence remains the risk factors associated with the greatest disease burden, accounting for 9.5% of the total burden in men and 6% in women [2]. More than one in six Australians continue to smoke each day, and tobacco smoking is responsible for the premature deaths of about 16,000 Australians each year [3]. Less than 10% of Australian smokers consistently deny any interest in quitting and approximately 40% report attempting to quit in the previous year [4]. Unfortunately unaided quit attempts have a low success rate of only 3-5% [5].

### Suitability of general practice for a quit smoking intervention

General practice is well suited for supporting smoking cessation. Around 85% of the Australian population visits a general practitioner (GP) at least once a year [6]. There is variation in reported rates of smokers presenting in general practice, with between 19.9% -35% of adult patients reported as currently smoking [7,8]. The familiar environment of general practice and the sustained relationships between patients and providers can provide an environment conducive to effective promotion of behavioural risk factor modification [9].

### Current general practice intervention

There is clear evidence that smoking cessation advice from a physician has an effect. The Cochrane review of 17 trials of brief advice versus no advice estimates that brief advice increases absolute rates of cessation at one year follow-up by about 2.5% compared to usual care [10]. This effect can be increased substantially if brief advice is combined with other evidence based support such as pharmacotherapy [11].

GPs in Australia as elsewhere have been encouraged by clinical practice guidelines [11] to offer smoking cessation advice and support, and some have attended training [12]. Despite this the number of patients who report receiving advice on smoking cessation from GPs is low [13]. In an Australian study of GPs' use of evidence-based approaches only 32% provided written materials and 28% set a 'quit date' [14]. Barriers raised by GPs to engaging in greater efforts in smoking cessation include: perception of lack of effect; lack of GP time; lack of GP skills; reluctance to raise the issue due to perceived patient sensitivity about smoking; and perceived lack of patient motivation [15].

### Quitline referral

An alternative to in-practice support from the GP is for GPs to identify smokers, provide brief advice and actively refer interested patients to the telephone Quitline. A study in Australia which compared standard in-practice management to this active referral to Quitline has shown that at 3 month follow up patients randomised to the referral intervention had a higher rate of sustained abstinence (12.3% compared with 6.9%). At 12 month follow-up patients in the referral intervention had a higher rate of sustained abstinence (6.5% compared to 2.6%), however this did not reach statistical significance [16]. The researchers concluded that GPs referring smokers to an evidence based telephone cessation service can result in increased cessation.

### Practice nurses and cessation support

An innovative model for enhanced smoking cessation support is provision of advice in the practice by general practice nurses. Practice nursing is rapidly emerging in Australia and is making a considerable contribution to capacity in primary care [17].

In Australia the practice nurse workforce has grown rapidly since 2003. Almost 60% of Australian general practices now employing a practice nurse [18] and practice nurses are increasingly regarded as core members of general practice teams [19]. The Australian Government has committed over $A230 million to support practices to employ practice nurses, however, their potential impact has been constrained by poor role descriptions, inadequate funding models, negative GP attitudes and unclear legal implications of the nursing role [20].

Although consumers support the practice nurse role in principle, there is no research to date on consumer acceptability of specific practice nurse interventions [21]. There is also a need for trials to test the impact of practice nurse interventions to ensure that the significant investment being made in expanding the practice nurse workforce achieves maximum impact on improving quality of care and patient outcomes [22]. Face-to-face support for smoking cessation provided within the practice primarily by a trained practice nurse may appeal to different groups of smokers who are less likely to use a telephone service such as people from culturally and linguistically diverse backgrounds (CALD). Support in the practice has the potential to be even more effective than referral to an outside service, given the familiar environment and setting of the practice within the local community [9].

Several studies have explored the effectiveness of involving the practice nurse in supporting smokers to quit [23-31]. In a study by Vetter et al there was a significant benefit at six month follow up [26]; another study demonstrated a significant reduction in smoking status [29] and a third study showed a reduction in the number of cigarettes smoked per day [28]. All other studies showed no significant difference. Limitations of these studies included the low uptake of the nursing intervention [23], research designs that provided only a one off nurse consultation and a lack of follow-up [24]. Additionally, there were low retention rates amongst smokers in these studies. The difficulties in retention of this group as study participants may have been responsible for the small effect sizes and lack of significance seen in some studies [32].

### Cost effectiveness of smoking cessation interventions

Smoking cessation strategies have been shown to be highly cost effective compared to many pharmacological, surgical and hospital treatments or services [33]. A recent systematic review of studies in a range of settings adjusted for variation in program effects and costing methods found cost effectiveness ratios ranged from US$490 to $US15280 per life-years saved (LYS) in different settings [34].

Face to face interventions are the most common strategies. A recent review of cost effectiveness studies for such face to face health behaviour interventions addressing smoking cessation found favourable cost effectiveness ratios for smoking cessation programs compared to preventative pharmaceutical and invasive interventions [35].

More intensive interventions may be more effective but also more costly [10]. Many studies omit disadvantaged populations which are known to have higher levels of smoking [10]. Health gains are likely to be larger in such groups. Hence it is proposed that although more intensive interventions may be more costly, cost effectiveness will still be very favourable as a result of the high health gains. The cost effectiveness analysis in this study will compare the more intensive interventions to usual care.

### Aims and objectives

This study will test the uptake and effectiveness of enhanced in-practice support for smoking cessation. The in-practice intervention (**Quit with Practice Nurse**) involves flexible support for quitting provided primarily by the practice nurse in partnership with the patient's GP and the Quitline. The number and diversity of smokers receiving intensive intervention will be optimised by offering a flexible package of support from the nurse, GP and Quitline to match the patient's needs. The rationale is that delivering more integrated and intensive quitting support will be more effective and offering flexibility in service provision will reach more smokers from a wider range of demographic, socioeconomic and cultural backgrounds.

The impact of the 'Quit with Practice Nurse' intervention will be compared contrasted with an alternative intervention group as well as with a control group. The alternative intervention is referral to an evidence based telephone support service (Quitline Referral Intervention). The control group is usual care by the GP (control group). Referral to a specialized cessation service such as the Quitline represents the major alternative approach to supporting cessation. An important strength of this study is the comparison of the new approach to both a referral model and usual care.

